### **Assessment of Efficacy**

| Primary endpoint                         | Outcome Measure                                                    |
|-------------------------------------------------|---------------------------------------------------------------------------|
| Percentage change in fasting colonic volume     | Difference in mean response between arms                                  |
| Secondary endpoints                      | Outcome Measure                                                    |
| Change in whole gut transit time                | Difference between treatment arms by ranking, unless normally distributed |
| Percentage change in fasting colonic gas volume | Difference in mean response between arms                                  |
| Change in fasting breath hydrogen               | Difference in mean response between arms                                  |
| Change in fasting breath methane                | Difference in mean response between arms                                  |

## **GOOD CLINICAL PRACTICE**

The study will be performed according to Good Clinical Practice principles. The volunteer study will undergo submission through the University of Nottingham Research Medical School Research Ethics Committee. All volunteers will give written informed consent. Their names will be entered into a subject log in the Trial Master File and a unique alpha numeric study code assigned. A simple Case Report Form will be kept for each volunteer.

## **ADVERSE EVENTS**

We do not expect any adverse events following this intervention with a food supplement. Previous studies have used a greater OF dose without reporting adverse events.

Should a Serious Adverse Event occur it will be noted, dealt with according to SOPs and reported to the Ethics Committee.

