**Version 1.0 16th July 2014**

### BACKGROUND AND RATIONALE

Oligofructose (OF) is a fructose-based oligosaccharide and defined in the EU as a dietary fibre. Enzymatically derived from the longer chain inulin, extracted from chicory, it is commonly used in processed food to improve mouth feel in fat-free products. OF is poorly digested and absorbed in the small bowel so passes to the colon where it is fermented by the bacteria usually resident in the colon, termed the microbiota. Its presence in the colon alters the composition of the microbiota, with reported potential benefits to health, leading to its description as a 'prebiotic'.

Recently, however, such poorly digested carbohydrates grouped together by the term FODMAP (fermentable oligo-, di-, mono-saccharides and polyols) have been proposed to exacerbate symptoms of irritable bowel syndrome (IBS) such as abdominal discomfort and bloating. Dietary exclusion of foods containing FODMAPs, such as wheat, dairy and certain fruit and vegetables, has been proposed as a treatment for IBS, with some evidence to support this. FODMAPs are thought to induce symptoms either by drawing water into the small bowel by osmosis, or through gaseous distension of the large bowel, or a combination of these combined with metabolite effects on motility.

The metabolic products of bacterial fermentation are short-chain fatty acids (SCFAs) and gases, such as hydrogen and methane. All of these can become substrates for growth of other bacteria, leading to a complex ecosystem. The SCFA butyrate provides nutrition to colonic epithelial cells, a phenomenon that has created interest in the role of butyrate, and the microbiota, in colon cancer, inflammatory bowel disease and functional gastrointestinal disorders. Recently butyrate has been shown to influence the development of colonic neurons, with potential effects on colonic motility and transit of luminal contents through the bowel. Thus, there appears to be a potential interaction between the colonic microbiota, complex carbohydrates in the diet and gastrointestinal transit with the suggestion of a possible effect on luminal serotonin levels. It is currently unclear how long a change in diet takes to alter the microbiota, but changes have been observed within a day of radical alteration in carbohydrate content of the diet.

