### Description

**A.** Maltodextrin, 7 gram serving taken 2 times daily for 7 days. Maltodextrin is a long-chain glucose polysaccharide, marketed by the Hut group, (Northwich, UK). The Material Safety Data Sheet for Maltodextrin lists no known side effects.

**B.** Oligofructose, 7 gram serving taken 2 times daily for 7 days. Oligofructose as Orafit P95® is manufactured, marketed and sold in the EU by Beneo, Germany. It is not considered to have any side effects in the doses proposed.

Both products will have a small amount of Carmine Red food dye - E120 - added to the supplement container. This will be approximately 5 grams of red powder in approximately 200 grams of supplement. Carmine Red is not absorbed by the bowel and has no side effects. It is used as a marker of whole gut transit. Its addition to the supplement will improve masking by making both powders pink, and will aid compliance. Carmine Red is of animal origin and not suitable for vegetarians. A similar process was approved by the University of Nottingham Medical School research ethics committee for the 2013 pilot study (A11072013 SCS MRI).

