### **Stopping rules and discontinuation**

Given the short time frame of the study there will be no planned stopping rules.

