### **Randomisation and Blinding**

Participants will be allocated to a treatment group according to a randomization schedule generated by an independent member of staff at the SPMMRC or NDDC using the online program [www.randomization.com](http://www.randomization.com). Randomization will be 1:1 in blocks of 6 to prevent imbalance between groups.

Participants, investigators and analysts will be blind to treatment allocation until analysis of the primary and secondary endpoints is complete. The intervention supplements are both white powders which are indistinguishable. They will be supplied in opaque containers with the gross weight recorded on the side. Labelling will be completed by members of NDDC/ SPMMRC staff not directly involved with the study.

The code will be kept by the Chief Investigator in a sealed envelope and on a password

protected computer not accessible by the study team. No adverse events directly relating to the study product are expected. Should a serious adverse event occur the intervention will be discontinued without any need to unblind as the supplement will have no bearing on subsequent management.

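### The protocol gives a recording rule for serious adverse events only and collects no abdominal symptoms, so non-serious intolerance of the supplement may be missed

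*Protocol*

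**What the plan says.** The Adverse Events section of the protocol makes three statements. None are foreseen: "We do not expect any adverse events following this intervention with a food supplement". The support offered is that "Previous studies have used a greater OF dose without reporting adverse events". The one procedure is "Should a Serious Adverse Event occur it will be noted, dealt with according to SOPs and reported to the Ethics Committee". Nothing is said about events that are not serious.

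The product sections take the same line. Under Description, the active supplement is "Oligofructose, 7 gram serving taken 2 times daily for 7 days", followed by "It is not considered to have any side effects in the doses proposed". Known Side Effects says that neither product is associated with any.

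The Background describes the class of carbohydrate differently: "FODMAPs are thought to induce symptoms either by drawing water into the small bowel by osmosis, or through gaseous distension of the large bowel". It does so while discussing IBS, and the Exclusion criteria remove people who meet Rome III criteria for IBS.

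On data collection:
- The primary, secondary and exploratory endpoints are colonic volume, transit, gas volume, breath gases, and urine and stool measures. None is a symptom or tolerability measure.
- The descriptions of Visits 1 to 5 contain no tolerability questions.
- The Days 8 – 13 section plans at least one attempted contact to talk over problems, and does not say that the answers are written down.
- Compliance accepts supplement use of 70 to 140% by container weight, without asking why servings were missed.
- Sample Size and justification replaces withdrawals and dropouts, and neither it nor the section on removal of participants asks for the reason.

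**The concern.** A prediction that no events will occur is not a reason to leave out the means of seeing them. Here the prediction stands beside a Background that gives two routes by which this class of carbohydrate is thought to produce symptoms. If nobody asks about bloating, pain or wind, the report may contain no such events simply because none were sought. The support quoted in the Adverse Events section has the same weakness: as worded, it says that earlier studies did not report events, not that they looked and found none.

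Two things are at stake. One is the safety description of 14 g/day in these volunteers. The other is interpretation of the comparison between arms. If participants on oligofructose missed servings or left because of discomfort, the 36 complete data sets would over-represent those who tolerate it, and nothing collected would reveal this. Neither symptoms nor reasons for leaving can be reliably recovered after the week is over.

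**Working it through.** The protocol states no symptom rate or tolerability figure, so there is no number of its own to reproduce. The check is a reading of the text plus some arithmetic for scale.

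**Step 1. Where could a non-serious symptom be recorded?**

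| Place in protocol | Provision for non-serious symptoms |
|---|---|
| Adverse Events | None; the rule is for serious events |
| Endpoints (all three lists) | None |
| Visits 1 to 5 | None |
| Days 8 – 13 contact | Problems discussed; recording not stated |
| Compliance | Weight only; no reason for missed servings |
| Withdrawal and replacement | No reason required |
| Good Clinical Practice | A simple case report form; content not described |

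The last row and the contact on Days 8 – 13 might pick something up. Nothing guarantees it, or ensures that both arms are asked in the same way.

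**Step 2. How much under-dosing and dropout could pass without a reason?**

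- Planned dose: 7 g × 2 = 14 g/day. The lower compliance limit is 70%, and 0.70 × 14 = 9.8 g/day, so a participant could average 4.2 g/day less than planned and still count as compliant.
- Up to 45 recruited for 36 complete sets: 45 − 36 = 9 people, across both arms, could leave and be replaced with no cause on file.

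**Step 3. How many symptomatic participants might be involved?** The rate is assumed. With 18 per arm (Details of Trial Regimen):

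- at 10%: 18 × 0.10 = 1.8
- at 40%: 18 × 0.40 = 7.2

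That is about 2 to 7 people in the oligofructose arm.

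**Step 4. Would 18 per arm be enough to see anything if questions were asked?** The chance of at least one case in 18 is 1 − (1 − p)^18:

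| Assumed rate p | Chance of at least one case |
|---|---|
| 5% | 0.60 |
| 10% | 0.85 |
| 20% | 0.98 |
| 30% | 0.998 |

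Symptoms at 10% or more would therefore very probably appear.

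**Step 5. What would a count of zero mean?** If all 18 were asked and none reported a symptom, the one-sided 95% upper limit is 1 − 0.05^(1/18) = 0.153, or 15.3%. If they were not asked, the count carries no information and no limit applies.

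**Step 6. Could the arms be formally compared?** Only for large differences. By the normal approximation at two-sided 5% with 18 per arm, power is 0.32 for 10% against 30%, 0.55 for 10% against 40%, and 0.77 for 10% against 50%. Symptom data would therefore be descriptive.

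**The case against.** The best case for leaving the protocol as it is runs as follows. This is a seven-day physiology study of a food ingredient in healthy volunteers, and tolerability is not among its objectives. The Background speaks of symptoms in IBS, and IBS is excluded. Its language is tentative. The Hypotheses predict no difference between arms in colonic gas volume, and the pilot's volume increase was not explained by gas, so the protocol does not forecast a between-arm difference in the distension that it connects with symptoms. The amount of supplement taken is known from container weights. The case report form and the SOPs are not shown and may capture more.

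Much of this stands, and it rules out several stronger readings that a reader might infer:

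- *That the protocol says these carbohydrates cause discomfort and bloating.* It does not. It reports a proposal about IBS patients and a thought mechanism.
- *That intolerance will go unrecorded.* The text is silent on non-serious events and does not exclude them. Only that they may be missed is supported.
- *That dose-related intolerance is being hidden.* One oligofructose dose is studied, so at most a difference from maltodextrin could be seen.
- *That the greater rise in breath hydrogen predicted on oligofructose amounts to predicting symptoms.* The prediction on gas volume in the same list points the other way.
- *That the protocol contradicts itself on stopping.* "Given the short time frame of the study there will be no planned stopping rules" can be read as a statement about the trial, whereas "Should a serious adverse event occur the intervention will be discontinued without any need to unblind" concerns an individual participant's intervention. They operate at different levels and do not conflict.

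What does not stand is the inference that nothing need be collected. The mechanism sentence is not itself confined to IBS, and the protocol nowhere says that healthy people are exempt. Knowing how much supplement was taken does not tell why some was not. A statistical analysis plan could not supply data that the visits do not gather.

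**Conclusion.** The point holds in a limited form. The protocol states a recording rule for serious adverse events only, schedules no symptom questions, and asks for no reason when servings are missed or participants are replaced. Non-serious intolerance, and any difference in it between arms, may therefore be missed, and a report with no events would not show that 14 g/day was tolerated.

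The size rests on an assumed symptom rate. At 10% to 40%, about 2 to 7 of 18 oligofructose participants would be concerned; the documents give no rate, and the true figure may lie outside that range. The sample size, the primary analysis and the secondary endpoints are unaffected. The change should be made because the information cannot be reliably recovered later and is cheap to collect, but the trial's main comparison does not depend on it.

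Whether the no-side-effects statements are factually right cannot be judged from the protocol. They sit uneasily beside the Background and need reconciling with it.

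**What to change.** 1. In Adverse Events, state that all adverse events are recorded, serious or not.
2. Ask a short fixed set of abdominal symptom questions (pain, bloating, wind, change in stool), in the same words in both arms, at contacts that already exist: Visit 3 before the first serving, as a baseline; the contact during Days 8 – 13; Visit 4; and Visit 5.
3. Record the reason for missed servings and for every withdrawal, including participants who are replaced.
4. Tabulate symptoms, missed servings and withdrawals with their reasons by arm, over everyone who took any supplement. Present them descriptively, given the power in Step 6.
5. Reconcile the statements in Description, Known Side Effects and Adverse Events with the account of symptoms in the Background.

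These are changes to data collection and wording; no dose or rule of clinical management is touched. The cost is about one case report form page and a few minutes at each existing contact, with no new visit or staff. The drawback is that asking may prompt reporting. With identical wording and blinded arms, that should be equal in both, so it would raise the level of reported symptoms without favouring either arm.
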